### Statistical considerations and rational

Since this is a feasibility RCT, no formal sample size calculations have been undertaken as the study is not designed or powered to detect a statistically significant difference in efficacy between the two treatment arms, which is consistent with guidance from the National Institute for Health Research (NIHR) in the UK [68].

As the cohort study is independent of the RCT’s aim, it is intended to be hypothesis generating, and no formal sample size calculation has been undertaken for it. One hundred forty patients will be randomised in the RCT. At least 60% of patients attending a secondary care diabetes clinic could be eligible for recruitment and based on the results of our previous work, showing an OSA prevalence of 65% in patients with T2D [15], it is expected that up to 500 patients will need to be registered into the observational cohort study and assessed for OSA to reach 140 participants with confirmed OSA eligible for randomisation in the RCT.

### Statistical analysis

The primary comparison groups will be composed of those treated with CPAP versus those not receiving CPAP. In the first instance, all analyses will use the intention to treat principle.

Analyses of outcomes will primarily take the form of simple descriptive statistics (e.g. proportions and percentages, means and standard deviations) and, where appropriate, point estimates of effect sizes (e.g. mean differences and relative risks) and associated 95% confidence intervals.

For the tertiary objectives, the full cohort will be analysed.

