### Randomisation

Eligible participants for the RCT will be randomised in a 1:1 ratio to either CPAP or no CPAP. A stratified block randomisation method will be used within the computerised randomisation system to ensure balance in the treatment allocation over the following variables: ethnicity (White Europeans, others), gender (male, female), and severity of OSA (AHI 10– < 15, ≥ 15).

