### Outcome measures

The primary outcome measures are to:
Assess willingness of participants to be randomised,Assess willingness of clinicians to recruit participants,Assess follow-up rates and adherence/compliance rates,Provide data to inform the sample size for a substantive trial,Optimise the choice of outcome measures for a substantive trial.

The secondary outcome measures are:

To assess the impact of CPAP in patients with T2D on:
Measures of CKD including eGFR, cystatin-C, and albumin/creatinine ratio (ACR),Diabetes-related neuropathy (including painless and painful peripheral neuropathy, cardiac autonomic neuropathy, and peripheral autonomic neuropathy),Diabetes-related retinopathy and maculopathy,Metabolic parameters such as weight, HbA1c, blood pressure, and lipids profile.

The changes in the above-listed diabetes-related endpoints will be described as changes in the values of continuous variables or changes in categories for categorical variables.

The tertiary outcome measures are:
To explore the utility of different biomarkers in screening for OSA in patients with T2D,To explore the mechanisms via which CPAP might have an impact on diabetes-related complications,To assess the relationship between other sleep-related disorders, metabolic parameters, and vascular disease in patients with T2D,To build up a cohort of well characterised patients for longitudinal follow-up to inform us about the natural history of OSA, sleep-related disorders, and diabetes-related complications.

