### Feasibility criteria

Recruiting the proposed sample size within the planned time frames,Meeting the proposed time frames in regard to interpreting the sleep assessments and initiating patients on treatment (within 8 weeks from the registration),Achieving a follow-up rate ≥ 80% for randomised patients,Achieving a CPAP usage ≥ 4 h/night on ≥ 70% of nights in ≥ 80% patients randomised to CPAP treatment,Generating a mean and standard deviation regarding the predicted response to the intervention to allow sample size calculations for a substantive RCT.

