### Study assessments and follow-up

Following consent and checking eligibility, participants will have a baseline assessment (0 months), in which the following data will be collected:

Physical examination:
Height and weight measurements,Waist, neck and hip circumferences,Blood pressure.

Biochemistry:
HbA1c,Random lipid profile,Creatinine,Urinary ACR.A serum sample for the measurement of cystatin C will also be taken.

Quality of life:
Short Form Health Survey (SF-12) questionnaire.

Peripheral neuropathy:
Michigan Neuropathy Screening Instrument (MNSI) questionnaire,Short Form McGill Pain Questionnaire (SF-MPQ),Selected sites will also perform Sudoscan and Cardiac autonomic neuropathy (CAN) assessments.

Sleep apnoea, habits, duration, and quality:
One-night home-based sleep assessment using a portable multi-channel respiratory device approved for screening and diagnosing OSA (ApneaLink Air, ResMed),ESS,Berlin questionnaire,Morningness-Eveningness Questionnaire (MEQ),Pittsburgh Sleep Quality Index (PSQI).

Retinopathy

The evaluation of retinopathy will be assessed using 2 × 45 degrees’ digital retinal images per eye as per the English National Screening program guidelines [67].

The examinations and the questionnaires for the baseline assessment are described in the Supplementary File 1 in detail.

All patients in the RCT and cohort study will be contacted every 6 months by phone to enhance follow-up rates and to collect data about any new relevant developments and ensure continuation of consent and patient safety. Those in CPAP will be contacted more often as described above depending on compliance and also for the short term after CPAP initiation. The same data with the baseline visit will be collected at study-end (at up to 2 years from baseline). Table 1 summarises the procedure from registration to follow-up visits.

**Table 1 Tab1:** Outcome measures and assessments

Summary of assessments	Trial period			
	Baseline visit (0)	Allocation [1] RCT only	Follow-up (telephone)	Follow-up visit (2)
Time point	0	1 m ± 1 m	6 m, 12 m, 18 m ± 2 m	2 years ± 3 m

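### Secondary endpoints are framed as changes with simple mean differences; adjusting for baseline and strata would be more precise, and the SD to be passed on is not named

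*Protocol article*

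**What the plan says.** Under Outcome measures, changes in the secondary endpoints (kidney measures, neuropathy, retinopathy, metabolic parameters) "will be described as changes in the values of continuous variables or changes in categories for categorical variables". Under Statistical analysis: "Analyses of outcomes will primarily take the form of simple descriptive statistics". Where appropriate, these are joined by "point estimates of effect sizes (e.g. mean differences and relative risks) and associated 95% confidence intervals". That section mentions no covariates.

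Three other places bear on the point:

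- Randomisation: "A stratified block randomisation method will be used within the computerised randomisation system to ensure balance in the treatment allocation" over ethnicity, gender and OSA severity (AHI 10 to <15, ≥15).
- Study assessments and follow-up: "The same data with the baseline visit will be collected at study-end". Table 1 restricts SUDOSCAN and CAN testing to selected sites.
- Feasibility criteria: one criterion is "Generating a mean and standard deviation regarding the predicted response to the intervention to allow sample size calculations for a substantive RCT". Informing the sample size of a substantive trial is also listed among the primary outcome measures.

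**The concern.** Read together, the Outcome measures and Statistical analysis sections most naturally describe a difference between arms in mean change. That estimator fixes the weight on the baseline value at one. ANCOVA estimates the weight from the data and so is at least as precise in large samples. The baseline values are already collected and the stratification factors are known at randomisation, so the gain would be free.

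Two things are at stake. One is the width of the intervals for the secondary endpoints. The other is closer to the trial's purpose: an SD is one of the things the study must hand on. If it is the SD of change and nothing else, a team planning a baseline-adjusted definitive trial cannot work out the residual SD without the baseline to study-end correlation, and the article does not ask for that correlation.

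**Working it through.** **The plan's own figure.** Under Statistical considerations and rational: "One hundred forty patients will be randomised in the RCT". No formal calculation was made, and no effect size, SD, power or precision target is given. The 140 therefore cannot be re-derived and is used here only as an input.

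**Inputs from the article**
- 140 randomised, 1:1 (Randomisation).
- Follow-up target of at least 80% (Feasibility criteria): 140 × 0.80 = 112 analysed, 56 per arm.
- 95% confidence intervals (Statistical analysis).

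**Assumptions, not in the article**
- Equal SD σ at baseline and study end.
- Correlation ρ between the two, shown over 0.5 to 0.9.

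**Formulas**
- SD of change = σ√[2(1 − ρ)]
- Residual SD under baseline adjustment = σ√(1 − ρ²)
- CI width, change relative to ANCOVA = √[2/(1 + ρ)]
- Sample size, change relative to ANCOVA = 2/(1 + ρ)
- 95% half-width with 56 per arm = 1.96 × √(2/56) × SD = 0.370 × SD

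**Interval width with 112 analysed**

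| ρ | SD of change (σ) | Residual SD (σ) | Half-width, change (σ) | Half-width, ANCOVA (σ) | Change CI wider by |
|---|---|---|---|---|---|
| 0.5 | 1.000 | 0.866 | 0.370 | 0.321 | 15.5% |
| 0.7 | 0.775 | 0.714 | 0.287 | 0.265 | 8.5% |
| 0.8 | 0.632 | 0.600 | 0.234 | 0.222 | 5.4% |
| 0.9 | 0.447 | 0.436 | 0.166 | 0.161 | 2.6% |

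**Effect on a later trial.** Suppose that trial is analysed by ANCOVA but sized on the SD of change. It is too large by 2/(1 + ρ) − 1: 33% at 0.5, 18% at 0.7, 11% at 0.8 and 5% at 0.9. As an illustration, take an assumed difference of 0.3σ, 80% power and two-sided 5%, so that n per arm = 2 × (1.96 + 0.842)² × SD² / (0.3σ)²:

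| ρ | n per arm, SD of change | n per arm, residual SD |
|---|---|---|
| 0.5 | 175 | 131 |
| 0.7 | 105 | 89 |
| 0.8 | 70 | 63 |
| 0.9 | 35 | 34 |

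**Stratification factors.** In 2,000 simulated trials of 112 patients for each ρ, the change-score interval was compared with ANCOVA on baseline plus three binary factors unrelated to outcome. The ratio of mean widths was 1.13, 1.04 and 1.01 at ρ = 0.5, 0.8 and 0.9, slightly below the formula values of 1.155, 1.054 and 1.026. Non-prognostic factors therefore add nothing and cost a little. If the factors explained 5% of the remaining variance (an assumption), the interval would narrow by 1 − √0.95 = 2.5%.

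**Compatibility with reporting change.** If study-end Y is modelled as a + bT + gX, with T the arm and X the baseline, then Y − X = a + bT + (g − 1)X. The arm effect b and its standard error are identical, so the article's change scale can be kept.

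**The case against.** The strongest reply is that the article never says the estimates are unadjusted. An adjusted mean difference is still a mean difference, the effect measures are given as examples, and describing endpoints as changes sets a reporting scale that ANCOVA can also serve. A condensed article commonly leaves the covariate model to the full protocol or SAP. The RCT is explicitly not powered for efficacy, its progression criteria are feasibility measures, and a slightly tighter interval on a secondary endpoint alters none of them.

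Much of this stands, and it rules out several stronger readings that a reader might infer:

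- *The plan ignores baseline.* A change score uses the baseline value, only not with the best weight.
- *The plan commits to an unadjusted analysis.* That is the natural reading, but it is not written.
- *The SD passed on is the wrong one.* The feasibility criterion does not name the SD. The SD of change is right for a future change-score analysis and, under equal variances, conservative for an ANCOVA.
- *Chance baseline imbalance biases the comparison.* Under randomisation the difference in mean change is unbiased; imbalance affects precision.
- *Omitting the strata invalidates the intervals.* If the strata are prognostic, the intervals tend to be conservative.
- *Raw ACR change will be distorted by skewness.* The article says nothing about the distribution of ACR and does not commit to a raw mean and SD for it.

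The point also cannot cover every outcome: willingness to be randomised, follow-up and adherence have no baseline value.

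What the reply does not remove is that the change scale is stated rather than left open, that the stratification factors do not reappear in the analysis text, and that the SD is a deliverable in its own right. Lack of power for efficacy does not dispose of that last point.

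**Conclusion.** The point holds as a minor improvement. For continuous secondary endpoints, a simple difference in mean change is valid but gives 95% CIs about 15% wider than baseline adjustment at ρ = 0.5, falling to about 3% at ρ = 0.9. The SD to be passed on is unspecified; the SD of change alone would oversize a baseline-adjusted definitive trial by 33% at ρ = 0.5 and 5% at ρ = 0.9.

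These sizes rest on equal variances at the two visits and on a correlation that the article does not give. For closely tracking measures the gain would be small. Two features could lower the correlation for some endpoints: the Table 1 footnote accepts ACR up to 12 months old and other routine biochemistry up to 3 months old, and the Discussion expects study-end visits both before and after 2 years, with at least 1 year of follow-up. The stratification factors improve precision only if prognostic. That the definitive trial will use baseline adjustment is also an assumption. No figure in the article is wrong on this point.

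**What to change.** For continuous secondary endpoints, state that the arm difference and its 95% CI come from ANCOVA on the study-end value (or on the change, which gives the same arm effect), adjusted for the baseline value, ethnicity, gender and AHI stratum (10 to <15, ≥15). Keep the simple descriptive summaries beside these estimates.

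For the sample-size deliverable, name the quantities to be reported for each candidate outcome: SD of change, SD of the study-end value, residual SD, and baseline to study-end correlation. A later team can then size either type of analysis.

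The cost is wording in the analysis plan. Every variable is already collected, and neither the number randomised nor the visit schedule changes. If the SAP or full protocol already says this, nothing further is needed.

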### Monitoring

#### Safety reporting (RCTs only)

The collection and reporting of adverse events (AEs) will be in accordance with the UK Policy Framework for Health and Social Care Research and the requirements of the Health Research Authority. The investigator will assess the seriousness and causality (relatedness) of all AEs experienced by the trial participant. Any trial-related serious AEs will be reported by the investigator or delegate on a trial-specific serious AE form to the Birmingham Clinical Trial Unit trials office, no later than 24 h after first becoming aware of the event.

#### Independent committee

A joint study oversight committee that comprises both Study Steering Committee and Data Monitoring Committee functions will be engaged for this trial. The role of the study oversight committee is to provide the overall supervision of the trial, monitor trial progress and advice on scientific credibility.

### Ethics approval and consent to participate

Patients will be approached by their clinical care teams and then consent for the cohort study will be obtained and baseline assessments performed by appropriately trained research nurses as per the delegation log. If eligible for the RCT, a further informed consent will be obtained by post or in person and the randomisation visit can be performed either at their local research centre or by telephone.

The study will be performed in accordance with the recommendations guiding physicians in biomedical research involving human subjects, adopted by the 18th World Medical Association (WMA) General Assembly, Helsinki, Finland, 1964, amended by the 48th WMA General Assembly, Somerset West, Republic of South Africa, 1996.

The trial will be conducted in accordance with the Research Governance Framework for Health and Social Care, the applicable UK Statutory Instruments (which include the Data Protection Act 2018 and Human Tissue Act 2008), the EU General Data Protection Regulation 2018, and the principles of Good Clinical Practice. Written informed consent will be provided by all patients prior to any trial-related procedures. Participants will be free to withdraw from the trial at any time without any effect on their standard of care.

## Discussion and conclusions

SLEEP T2D is an observational cohort study with a subset of participants included in a feasibility RCT of a CE marked medical device used within its intended purpose. The outcome of this study will guide the design of a future RCT that might have significant impact on reducing the burden of T2D microvascular complications. In addition, the observational cohort study will provide novel hypothesis generating data that might lead to future RCTs to improve diabetes-related outcomes.

This study has several strengths including its novelty and the multicentre and randomised design. It also uses a pragmatic approach to CPAP treatment and the study population are very well characterised and phenotyped. However, the study has its limitations, including the unblinded design, but most of the study outcomes are not based on patient reporting and the decision not to have sham CPAP was pragmatic and discussed above. The study has now finished recruitment and all patients are currently in follow-up. As a result of the disruption caused by COVID-19 pandemic and the focus on COVID-19 research by the participating NHS trusts and the need to move the feasibility RCT forward to apply for funding for the full RCT (if applicable), we have submitted an amendment that has been approved to collect study-end data as soon as it is practical and allowed by the NHS trusts. This means that for some study participants, the study-end visit will be after less than 2 years follow-up and for others it will be more than 2 years. We aim to start the study end visits from January 2021 in the centres that allow us. We expect all patients to have at least 1 year follow-up by the time they have the study end visit.

## Data Availability

Not applicable.

## Abbreviations

OSA: Obstructive sleep apnoea
AHI: Apnoea-Hypopnoea Index
T2D: Type 2 diabetes mellitus
PARP: Poly (ADP-ribose) polymerase
PKC: Protein kinase C
AGE: Advanced glycation end products
CKD: Chronic kidney disease
PN: Peripheral neuropathy
STR: Sight-threatening retinopathy
eGFR: Estimated glomerular filtration rate
CPAP: Continuous positive airway pressure
RCT: Randomised control trial
EDS: Excessive daytime sleepiness
ESS: Epworth Sleepiness Scale
HbA1c: Haemoglobin A1c
ACR: Albumin/creatinine ratio
SF-12: Short Form Health Survey
MNSI: Michigan Neuropathy Screening Instrument
SF-MPQ: Short Form McGill Pain Questionnaire
CAN: Cardiac autonomic neuropathy
MEQ: Morningness-Eveningness Questionnaire
PSQI: Pittsburgh Sleep Quality Index
AE: Adverse event
